### Intervention

The RunFitCheck intervention (in Dutch), is an intervention developed according to an evidence-based (intervention mapping) and practice-based (running experts) approach to stimulate injury-preventive behavior among novice runners (see Multimedia Appendices 1, 2, and 3). The development of the intervention was a collaboration with running experts and the target group and is described in detail in Kemler, Valkenberg, and Gouttebarge (in press).

A range of experts was consulted in the development of this intervention: a sports physician who is head of the medical commission of the RDRA and related to the RDRA as a sports physician since 1977; a sports physiotherapist specialized in running since 1992; 2 running coaches, of whom 1 is a fulltime running coach since 2002 and coach of both successful Dutch top athletes and recreational athletes, and a second coach who has over 40 years of running experience, was a top athlete himself, coaches recreational athletes, and has worked for the RDRA for 20 years; and a researcher specialized in sports injuries who performed the running-related literature review that laid the foundations for this study. These experts were consulted and their feedback combined with literature on the use of running apps (Romeyn, Kemler and Huisstede, in press). Through the consultation and research process, 2 main dimensions in the risk for RRIs, namely the physical load-taking capacity of runners and motivation of runners to achieve their running goals, were identified. Across these 2 domains, runners can be classified in 4 categories: (1) a low physical load-taking capacity and a low goal-orientation, (2) a low physical load-taking capacity and a high goal-orientation, (3) a high physical load-taking capacity and a low goal-orientation, and (4) a high physical load-taking capacity and a high goal-orientation. In order to classify runners within 1 of the 4 categories, they will answer 6 questions (Multimedia Appendix 4). Depending on their answers and related classification, runners will directly receive tailored advice on the website for achieving an optimal running practice. Examples of advice will be related to strength exercises, running technique improvement, and use of a training schedule. Advice about a warm-up will also be given. After receiving the tailored advice, runners can leave their email address on the website so that they will receive a tailored running schedule and a strength exercise schedule every week. The RunFitCheck intervention will be made available to the participants within the intervention group. Substantial efforts have been made to develop an intervention that provides practical injury prevention advice.

### Running as Usual

The participants in the control group will perform their running activities as usual. The RunFitCheck website is not secured with a log-in code for the intervention group as the research team wants to avoid any additional barriers for participants to use the intervention. Participants in the control group will be able to visit and use the website alongside those in the intervention group; however, they will not be actively encouraged to do so during the study period. In order to determine whether control group participants accessed RunFitCheck, data from control group participants pertaining to websites they visit during the study period will be collected. Control group participants who have visited RunFitCheck will be excluded from the analyses.

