### Participants and Recruitment

The group of participants will consist of novice runners. The inclusion criteria are being aged 18 years and older, considering oneself as a beginner, a slightly experienced runner, or a rather experienced runner, and having less than one year of running experience when a runner considers oneself as an experienced or very experienced runner. Participants do not have to be a member of a running club. Participants will be recruited via social media networks (Facebook, websites, Twitter, LinkedIn, and newsletters) of the participating organizations (Dutch Consumer Safety Institute, Runner’s World, and Royal Dutch Running Association [RDRA]) and will be able to preregister for the study in the 2 months prior to the start of the study.

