### Recruitment of Participants

For the study results to be meaningful, 1000 novice runners need to be enrolled. To enhance enrollment and the possibility to preregister for the study, several strategies will be used, such as social media (Facebook, LinkedIn, and Twitter), newsletters from the RDRA (digital), and the magazine Runner’s World (in print and digital). Preregistration will be possible by filling in a Web-based form on the website of the Dutch Consumer Safety Institute. Preregistration for the study will be advertised on Facebook and Twitter.

Social media has been previously utilized by the research team to recruit runners with close to 1000 participants recruited within 2 weeks. Respondents were recruited via social media, such as Facebook and Twitter, and they were invited to give their opinion on running, running injuries, and injury prevention. As the research team recruited nearly 1000 runners within 2 weeks, they are confident that they will achieve 1000 participants in this study with similar recruitment strategies.

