### Adherence to the Study

To provide an incentive to complete all components of the study, enrolled participants who complete all questionnaires will be entered into a draw to win a €200 gift voucher for running clothes. This strategy might enhance the respondents’ adherence to the study. The gift voucher for running clothes will be a gift from RDRA. RDRA supports the RunFitCheck intervention but is not otherwise related to this study.

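### The intervention site is left open to controls; their visits either dilute the contrast or trigger a one-arm exclusion, and an unlisted emailed link would reduce both harms

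*Protocol article*

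**What the plan says.** Running as Usual explains the lack of access control: "The RunFitCheck website is not secured with a log-in code for the intervention group as the research team wants to avoid any additional barriers". It accepts the consequence: "Participants in the control group will be able to visit and use the website alongside those in the intervention group". Three measures follow. On encouragement, the text says of controls that "they will not be actively encouraged to do so during the study period". On detection, "data from control group participants pertaining to websites they visit during the study period will be collected". On handling, "Control group participants who have visited RunFitCheck will be excluded from the analyses".

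Statistical Analysis says that relative risks with 95% confidence intervals will follow the intention-to-treat principle. Sample Size and Allocation gives 384 per group for 80% power at a significance level of .05, and 1000 to be approached after allowing for 85% response and 10% dropout. It makes no allowance for controls using the intervention.

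The Introduction names the Dutch Consumer Safety Institute as developer of RunFitCheck. Participants and Recruitment lists that institute, Runner's World and the RDRA as recruitment channels, and Recruitment of Participants adds: "Preregistration will be possible by filling in a Web-based form on the website of the Dutch Consumer Safety Institute". Procedures shows that every participant's email address is collected and that the questionnaires are sent by email.

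**The concern.** The website is the intervention: a runner answers six questions, gets tailored advice at once, and can leave an email address for weekly schedules (Intervention). A control who reaches the site can therefore receive everything the intervention arm receives. Controls come from the audiences of the developer and of a declared supporter, so some such visits are foreseeable.

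The only reason given for open access is to spare participants a log-in. That aim does not require a site that controls can also use, because a personal link sent by email needs no code.

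Once a control has visited, both outcomes under the plan are unfavorable. If the visit is missed, a partly treated person counts as running as usual. If it is detected, that person leaves the control arm because of something done after randomization, with no matching rule in the intervention arm. Running as Usual and Statistical Analysis then describe two different analysis sets.

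**Working it through.** **Inputs from the article.** 384 per group, 80% power, significance level .05, a 10% difference (read as 10 percentage points), 85% response, 10% dropout.

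**Assumptions.** Two-sided test; control rate 50% (not stated); visiting controls gain the full 10 points; a share c of controls visits, with c = 10% or 20% (not stated).

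**Reproducing the sample size.** n per group = (1.96 + 0.842)² × [p0(1 − p0) + p1(1 − p1)] / (p1 − p0)². At 50% v 60% this is 7.849 × (0.25 + 0.24) / 0.01 ≈ 385; the pooled-variance version gives 388. Both agree with 384. The total is 768 / (0.85 × 0.90) = 1004, against 1000. The match does not establish the control rate: 40% v 50% gives the same n.

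**Visitors missed or kept.** The control rate becomes p0 + c(p1 − p0). Power = Φ{[d − 1.96·√(2p̄(1 − p̄)/n)] / √([p0(1 − p0) + p1(1 − p1)]/n)}, where d is the difference that remains, p0 the control rate after visits and p̄ the mean of the two rates.

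- c = 0: (0.10 − 0.0704) / 0.0357 = 0.83, power 80%.
- c = 10%: control rate 51%, d = 0.09; (0.09 − 0.0703) / 0.0357 = 0.55, power 71%.
- c = 20%: control rate 52%, d = 0.08; (0.08 − 0.0702) / 0.0357 = 0.27, power 61%.

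Restoring 80% power would take 478 or 604 per group, against 388 by the same formula without contamination.

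**Visitors all detected and excluded.** The difference stays at 10 points if exclusion is unrelated to outcome, and the control arm shrinks to 346 (c = 10%) or 307 (c = 20%). Power is 77.5% or 74.9%.

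**Bias from the exclusion.** Suppose the intervention has no effect and a share p of runners would change behavior in either arm. Let visiting be r times as likely among those who would change. With p = 20%, c = 20% and r = 2, the visit probability is 0.20 / (0.20 × 2 + 0.80) = 0.167 among non-changers and 0.333 among changers. The remaining control rate is 0.20 × 0.667 / (0.20 × 0.667 + 0.80 × 0.833) = 0.167, so the relative risk is 0.20 / 0.167 = 1.20 with no true effect. Over p = 20% or 50%, c = 10% or 20% and r = 1.5 or 2, the false relative risk runs from 1.02 to 1.20. All of these inputs are assumed.

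**Sensitivity to the control rate.** At 20% v 30% with 384 per group, power without contamination is about 89% [(0.10 − 0.0613) / 0.0310 = 1.25]. It falls to 82% or 72% if 10% or 20% visit and are kept, and to 88% or 85% if they are all detected and excluded.

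**The case against.** The choice is disclosed and reasoned. Procedures says the evaluation is deliberately not in an experimental setting, and the plan records control visits and removes visitors. Lack of encouragement is therefore not the only protection, and a reader who takes 71% or 61% as the power of the planned analysis goes too far: those figures need visitors to be missed or kept. With perfect detection the loss is small. All these figures also use 384 per arm, whereas Statistical Analysis restricts each comparison to people not already taking that measure at baseline, so they show the size of the loss and not the power of the actual analysis set. This all stands.

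A reader might also infer that the recruiting organizations will advertise RunFitCheck during follow-up. The article does not say so; it says they recruit and that preregistration is advertised. Nor does it say whether the site address is listed or publicized. A further inference, that a follow-up question would reveal the site to controls, has no basis because the questionnaire wording is not shown.

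Finally, a personal link can be forwarded, and a token log would credit a forwarded visit to the intervention participant who owns the link. The link therefore cannot guarantee a clean control arm or by itself identify the controls who got in.

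What the objection does not remove is the cost of the safeguard. Exclusion limits dilution only by departing from intention to treat, and it works only as well as detection does.

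**Conclusion.** The point holds as a worthwhile and inexpensive design improvement. Open access rests on avoiding a log-in, which a no-log-in personal link would also avoid. Each control visit either weakens the contrast or removes a person from one arm after randomization. At 50% v 60% with 384 per arm, 10% or 20% of controls visiting brings power to 71% or 61% if they are missed or kept, and to about 78% or 75% if all are found and excluded. In the second case the relative risk can also be biased away from 1, by an amount that depends on who visits. The control rate, the visiting rate and the benefit to visitors are assumptions; the article gives none of them.

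The documents do not support the stronger reading that contamination will occur at a known level or that a personal link would eliminate it. Separately, Adherence to the Study says "RDRA supports the RunFitCheck intervention but is not otherwise related to this study", while Participants and Recruitment counts the RDRA among the participating organizations. That is an editorial inconsistency to correct and has no bearing on the size of this problem.

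**What to change.** 1. For the study period, serve RunFitCheck at an unlisted, non-indexed address and send it to intervention participants as a personal email link with no log-in.
2. Have the Dutch Consumer Safety Institute, Runner's World and the RDRA hold back RunFitCheck promotion until the month 5 questionnaires close.
3. Keep controls who visit anyway in the primary intention-to-treat analysis. Report how many visited, and exclude them only in a sensitivity analysis. Amend Running as Usual to agree with Statistical Analysis.

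Items 1 and 2 cost a web setting, a mail-merge link and about 5 months' delay in public promotion. They lower contamination without ruling it out. Item 3 costs power if visits are common (71% or 61% in the example above), which is the reason to pair it with items 1 and 2. The Results section reports that enrollment is complete and analysis under way; if so, only item 3 can still be applied to this trial, and the number of visiting controls should be reported with the result.

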**Methods:**

A randomized controlled trial with a follow-up period of 5 months will be conducted. The participants will be novice runners. At enrollment, participants will be asked to report injury-preventive measures they usually take during their running activities. After completing the enrollment questionnaire, participants will be randomized to intervention and control groups. The intervention group will have access to the RunFitCheck intervention; the control group will perform their running activities as usual. Participants will be asked to report retrospectively in detail what they have done regarding injury prevention during their running activities at 1, 3, and 5 months after enrollment. Descriptive analyses will be conducted for different baseline variables in the intervention and control group. Relative risks and 95% CIs will be used to analyze behavioral changes according to the intention-to-treat principle.

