Questionnaires will be administered at study commencement and at 1, 3, and 5 months post-commencement. In these follow-up questionnaires, participants will be asked to retrospectively report in detail what they have done in the past month(s) regarding injury prevention during their running activities and will be asked questions about their current injury-preventive behavior, running activities, and running injuries during running activities. The injury definition utilized in this study is “any physical complaint arising during a running activity that does not allow the participant to complete the activity or affects their ability to participate in future running activity” [14-17].

At 4 time points, a Web-based questionnaire will be sent by email to participants by the principal researcher, using the Web-based questionnaire system SurveyMonkey. When participants fail to complete a questionnaire, reminder notifications will be sent via email by the principal researcher using the Web-based questionnaire system SurveyMonkey 7 days after a questionnaire is due. A second reminder will be sent after 2 weeks.

The evaluation of the effectiveness of RunFitCheck will not take place in an experimental setting. Participants in the intervention group will be given access to the intervention, but no further conditions will be applied to the use of the intervention. In the questionnaires at 1, 3, and 5 months, the intervention group will be asked about their use of the intervention, attractiveness of the intervention, behavioral actions they take after being exposed to the intervention, their intention to use this intervention again, and how they would want to be informed about this intervention. If participants indicate they do not use the intervention, they will be asked to give detailed information about why they do not use the intervention.

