### Statistical Analysis

Descriptive analyses (mean [SD], frequency, and range) will be conducted for the different baseline variables in both study groups. To evaluate the success of the randomization, baseline variables will be analyzed for differences between the intervention and control group (chi-square test, independent *t* test, and Mann-Whitney test).

Relative risks (RRs) and a 95% CI will be used to analyze behavioral change according to the intention-to-treat analyses: (1) using a (personalized) training schedule, (2) performing strength and technique exercises, (3) performing a warm-up. Participants who do not execute a certain injury-preventive measure at study commencement will be selected for analysis, since among these participants, most behavioral change can be expected. If there are any differences in descriptive characteristics at baseline (eg, differences in sex, age, or running experience), subanalyses for sex, different age categories, etc will be performed.

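### Control participants who visit the RunFitCheck website after randomisation are dropped from the analyses, with no matching rule in the intervention arm; this contradicts the stated intention-to-treat analysis and is expected, though not certain, to inflate the relative risk.

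*Protocol article*

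**What the plan says.** In the Protocol article, Running as Usual, the site has no log-in: "Participants in the control group will be able to visit and use the website alongside those in the intervention group". Controls are not encouraged to use it. Information on the websites they visit during the study period is collected so that such use can be detected, and the rule follows: "Control group participants who have visited RunFitCheck will be excluded from the analyses". It refers to the analyses in general and is not limited to a per-protocol or sensitivity set.

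The Statistical Analysis section states the opposite principle: "Relative risks (RRs) and a 95% CI will be used to analyze behavioral change according to the intention-to-treat analyses". The abstract agrees: "Relative risks and 95% CIs will be used to analyze behavioral changes according to the intention-to-treat principle".

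For the intervention arm, the Procedures section says that participants are given access, "but no further conditions will be applied to the use of the intervention". Those who do not use the site are asked why, and no rule removes them.

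Two further statements bear on the point. The Injury-Preventive Behavior section of the Methods divides each behaviour into preparatory acts, with searching for information as its example, and structural measures. The Statistical Analysis section restricts each behaviour's analysis to participants who do not perform that behaviour at study commencement.

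**The concern.** Intention-to-treat keeps randomised participants in their assigned arm whatever they do afterwards. This rule removes people from one arm because of something they did after allocation. By randomisation, the intervention arm holds a similar share of people who would have sought the site out unprompted, and they all stay in. The comparison is then between a whole arm and a selected part of the other, and randomisation no longer protects it.

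The selection is probably related to the outcome. A control who finds an injury-prevention website without being prompted is already seeking information, which the article counts as a preparatory act. If such runners adopt the behaviours more often, removing them lowers the control rate while the intervention rate stays where it was. An RR above 1 could then appear even if the site did nothing. The outcome at stake is the trial's primary one, and the target is a 10% difference, read here as 10 percentage points.

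**Working it through.** **The plan's own figures.** The point does not rest on the sample size, but the sample size fixes the scale. With two-sided alpha 0.05 (sidedness assumed), 80% power and 40% vs 50% (rates assumed, as the control rate is not given), the unpooled formula gives (1.960 + 0.842)² × (0.40×0.60 + 0.50×0.50) / 0.10² = 384.6 per arm, consistent with the stated 384. The total is 768 / (0.85 × 0.90) = 1004, against the stated 1000. Conversely, 1000 × 0.85 × 0.90 = 765, or about 382 per arm.

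**Bias with no true effect.** Let c be the share who would visit the site unprompted (equal in both arms by randomisation), pv their adoption rate and pn the rate in everyone else.

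- Intervention arm, all kept: c·pv + (1 − c)·pn
- Control arm after the exclusion: pn
- Apparent RR = [c·pv + (1 − c)·pn] / pn

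The RR exceeds 1 if pv > pn, equals 1 if pv = pn, and is below 1 if pv < pn. The article gives none of c, pv or pn, so every value below is an assumption.

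**False-positive rate.** I used a two-sided 5% z-test of two proportions (pooled SE for the critical value, unpooled for the spread), with n intervention and n(1 − c) control participants. Worked case with n = 382, c = 0.10, pv = 0.60, pn = 0.20:

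- Rates 0.24 vs 0.20, RR 1.20, controls analysed 343.8
- Pooled rate 0.2211, pooled SE 0.0308, unpooled SE 0.0307
- Upper tail Φ[(0.04 − 1.96 × 0.0308)/0.0307] ≈ 0.253; the lower tail is negligible

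**Analysed number.** Each analysis covers baseline non-performers only, and their share is not stated. I therefore show 382 per arm as an upper case and 191 per arm, assuming that half are non-performers. In each range the first figure is for pv = 50%, pn = 30% and the second for pv = 60%, pn = 20%.

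| Controls visiting (assumed) | RR, no true effect | False-positive rate, 382 per arm | False-positive rate, 191 per arm |
|---|---|---|---|
| 2% | 1.01-1.04 | 5.2-5.9% | 5.1-5.4% |
| 5% | 1.03-1.10 | 6.0-10.2% | 5.5-7.6% |
| 10% | 1.07-1.20 | 8.9-25.3% | 6.9-14.9% |
| 20% | 1.13-1.40 | 19.9-68.2% | 12.3-40.2% |

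The RR column does not depend on the analysed number.

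**Other assumptions.**

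- Higher base rate (70% vs 40%, 384 per arm): RR 1.075 at 10% visiting and 1.15 at 20%, with false-positive rates of 13.0% and 35.2%.
- Small gap (40% vs 30%, 10% visiting, 382 per arm): RR 1.03, false-positive rate 6.0%.
- Equal adoption (30% vs 30%): RR 1.00, 5%.
- Visitors adopting less (20% vs 30%): RR 0.98 at 5% visiting and 0.93 at 20%.

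**With every randomised control kept.** With no true effect, both arms have the same expected rate, so RR is 1.00 and the false-positive rate is 5%, whatever c, pv and pn are.

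**The case against.** The strongest defence is contamination. A control who uses the site has received the intervention, and keeping that person blurs the contrast. This is true, but the two errors differ in kind. Retention pulls the estimate towards no effect, whereas exclusion can create an effect where none exists. Leaving the site open was a deliberate choice, made to avoid barriers to use.

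A second defence is that an unseen full protocol or analysis plan may confine the exclusion to a secondary analysis. The point does not rest on silence, however. The article itself states both the exclusion and the principle it conflicts with, and qualifies neither.

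Three objections to the size and certainty do stand:

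- **Direction.** A reader might infer that the rule necessarily favours the intervention. The article has no data by visit status. Runners might look for advice because of complaints or injury, and their adoption could then be higher or lower.
- **Frequency.** A reader might infer that control visits are expected in number. The text allows visits and does not encourage them; it gives no rate. At 2% visiting the harm is negligible.
- **Denominator.** False-positive rates at 382 per arm overstate the risk for the planned analysis of baseline non-performers, which is why 191 is shown as well. The restriction might also narrow the gap between visitors and others.

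**Conclusion.** The contradiction is certain: an unqualified exclusion in one arm, based on behaviour after randomisation, is not intention-to-treat. It holds whatever the visit rate or the direction of bias, and it affects the primary outcome comparison.

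Inflation of the RR is the more plausible direction, because visitors act unprompted and information seeking is part of how behaviour is defined, but it remains an inference. Under the assumed adoption gaps, the bias ranges from trivial at 2% visiting to 2-4 percentage points at 10% and 4-8 points at 20%, against the 10-point target. The documents do not support a claim that the trial will show a spurious effect, or that its false-positive rate is any particular figure.

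The restriction to baseline non-performers is a separate matter. It uses a variable measured before allocation and applies to both arms, so it does not cause this problem.

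**What to change.** Delete the exclusion from the primary analysis. State that, within the subset defined at baseline, every randomised participant is analysed in the assigned arm, including controls who visited the site. Report the number and share of control visitors. If the analysis without them is wanted, present it as a labelled per-protocol sensitivity analysis, with a note that it is not protected by randomisation. A complier-average (instrumental-variable) estimate, using control visit data and intervention-arm use data, is optional and not needed to resolve the contradiction.

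The change is about one sentence and uses data already planned for collection. Its real cost is dilution. With assumed rates of 50% vs 60% and 10% of controls gaining the full effect, the control rate becomes 0.90 × 50% + 0.10 × 60% = 51%. The difference falls to 9 points, and power at 384 per arm falls from about 80% to about 71%. Both power figures would be lower in the smaller baseline subset. The article reports enrolment as complete and analysis as under way, so a larger sample cannot offset this. The loss should be acknowledged when the result is interpreted.
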